### Control: usual care

Participants in the control arm will receive EIPS usual care and standard discharge planning, with no structured peer-coaching sessions using MyBRANCHES provided. Services may provide variable psychoeducation and support (including peer support); this will be documented descriptively in implementation logs. Treatment as usual typically includes routine clinical follow-up with the primary clinician/care coordinator; medication review and management; *ad hoc* psychoeducation or relapse-prevention support; referrals to adult mental health services, primary care or private providers; and standard discharge-planning procedures. Treatment as usual varies across services, so site-level descriptions of standard care and discharge processes will be documented to support interpretation and reproducibility.

### Minimising contamination

Several strategies will be used to minimise contamination between trial arms. Peer coaches delivering the MyPREPED intervention will deliver the intervention only to participants randomised to the intervention arm. Although peer coaches may be employed directly through trial funding or embedded within participating services depending on local arrangements, their MyPREPED role will be distinct from any peer support provided as part of usual care, and they will not provide intervention content to control participants. Where peer support is available as part of usual care within some of the participating services, peer workers not involved in MyPREPED delivery will not receive training in MyPREPED procedures or access to the MyBRANCHES tool during the trial period. Intervention materials, including access to the MyBRANCHES progressive web application, paper workbooks and peer-coaching guidance, will be restricted to intervention participants. Services will be asked not to use MyBRANCHES in routine practice until trial completion. Any incidental exposure or potential contamination reported by participants, peer coaches or clinicians will be documented through session logs and qualitative interviews, and examined in sensitivity and process analyses.

### Outcomes

The trial will include a comprehensive set of implementation, effectiveness and economic outcomes assessed across multiple time points. Consistent with the study’s co-produced design, lived experience researchers, peer coaches, young people and transdisciplinary academic staff were involved in shaping outcome selection and prioritisation. For example, the primary effectiveness recovery outcome – RAS-DS score^
45
^ at 12 weeks – was co-selected with lived-experience partners, who identified its strong conceptual alignment with the MyPREPED content domains and its relevance to youth-led definitions of recovery. RAS-DS outcomes will be measured at baseline, 12 weeks post baseline (primary end-point) and 52 weeks post baseline. Secondary effectiveness outcomes include mental health-related quality of life (ReQoL-20),^
46
^ psychological distress (Kessler-10),^
47
^ well-being (My Life Tracker-5),^
48
^ general self-efficacy (Short-Form General Self-Efficacy Scale),^
49
^ social inclusion (Filia Social Inclusion Measure),^
50
^ service satisfaction (Client Satisfaction Questionnaire-8),^
51
^ health literacy (Single-Item Literacy Screener)^
52
^ and clinician-rated functioning (Social and Occupational Functioning Assessment Scale);^
53
^ general health-related functioning and quality of life will also be assessed for economic evaluation purposes only, using the SF-12.^
54
^ The primary implementation outcome is feasibility, which will be measured using the FIM^
41
^ at 12 weeks among participants in the intervention arm and peer coaches. Additional implementation outcomes comprise acceptability (Acceptability of Intervention Measure^
41
^); appropriateness (Intervention Appropriateness Measure^
41
^); adoption, fidelity, penetration, retention and usability (System Usability Scale^
55
^); safety, and indicators of sustainability and scalability, informed by the Intervention Scalability Assessment Tool framework. The economic evaluation will use a micro-costing approach to estimate the cost of the MyPREPED intervention. The purpose-built Resource Use Questionnaire (RUQ^
56
^) will measure participants’ use of health services and lost productivity, which will be monetised by attaching standard Australian unit costs. Outcomes for the economic evaluation will be utility values and quality-adjusted life-years derived from the Recovering Quality of Life – Utility Index (ReQoL-UI) and Short Form 6 Dimensions (SF-6D). A consolidated schedule of measures, summarising timing and instruments across all outcome domains, is presented in Table 2.

**Table 2 tbl2:** Outcome measures of the study Table 2 long description.

Outcome category	Item	Baseline	Post-intervention (12 weeks)	Follow-up (52 weeks)
Primary effectiveness outcome	Recovery Assessment Scale-DS (RAS-DS)^ 44 ^	✓	✓	✓
Secondary effectiveness outcomes	Recovering Quality of Life (ReQoL-20)^ a 47 ^	✓	✓	✓
	Short-Form General Self-Efficacy Scale (GSE-6)^ 50 ^	✓	✓	✓
	My Life Tracker (MLT-5)^ 49 ^	✓	✓	✓
	Filia Social Inclusion Measure (F-SIM-16)^ 51 ^	✓	✓	✓
	Client Satisfaction Questionnaire-8 (CSQ-8)^ 46,52 ^	✓	✓	
	Short Form Health Survey (SF-12)^ a 55 ^	✓	✓	✓
	Single-Item Literacy Screener (SILS) (ref)^ 53 ^	✓	✓	✓
	Kessler-10 (K10)^ 48 ^	✓	✓	✓
	Social and Occupational Functioning Assessment Scale (SOFAS) – clinician-reported^ 54 ^	✓	✓	
Primary implementation outcome	Feasibility of Intervention Measure (FIM)^ 42 ^		✓	
Secondary implementation outcome	Acceptability of Intervention Measure (AIM)^ 42 ^		✓	
	Intervention Appropriateness Measure (IAM)^ 42 ^		✓	
	Administrative metrics	✓	✓	✓
	System Usability Scale (SUS)^ 56 ^		✓	
	Qualitative interviews		✓	
Economic outcomes	Brief Resource Use Questionnaire (RUQ) service use (e.g. emergency department presentations, hospital admissions, crisis service use, other service use)^ 57 ^	✓	✓	✓
	Medication: Brief Resource Use Questionnaire (RUQ) medications list – clinician-reported,^ b 57 ^ and client-reported^ c ^	✓^b^	✓^b^	✓^ c ^
Safety outcomes	Adverse events; qualitative reports on distress		✓	✓

a. Economic outcomes.

b. Clinician-reported.

c. Client-reported.

### Sample size and power

The total planned sample size is 260 participants (130 per arm). This sample size aligns with the original calculation outlined in the protocol and statistical analysis plan, and was based on detecting a small-to-moderate effect (seven-point difference in RAS-DS score, s.d. = 15, Cohen’s *d* = 0.47) on the primary effectiveness outcome while ensuring adequate precision for feasibility and implementation estimates. We assumed a seven-point between-group difference on the RAS-DS at 12 weeks, corresponding to a small-to-moderate effect size (Cohen’s *d* of approximately 0.47) using a conservative s.d. of 15. This assumption was informed by prior RAS-DS psychometric studies in Australian community mental health samples, which report somewhat smaller standard deviations,^
42,57
^ and was chosen to ensure adequate power for effectiveness estimates. The sample size calculation also assumes up to 20% attrition, an intracluster correlation coefficient of 0.02 (consistent with published methodological guidance showing intracluster correlation coefficients of 0.01–0.05 for patient-reported mental health outcomes^
58
^) and an average cluster size of 20, with parameter optimisation undertaken to confirm feasibility under these assumptions. Full details of the sample size modelling and assumptions are provided in the statistical analysis plan (available via the Australian and New Zealand Clinical Trial Registry, under identifier ACTRN12626000169347).

### Statistical analysis

All analyses will follow the intention-to-treat principle, with a complementary per-protocol sensitivity set defined *a priori* in the statistical analysis plan. Continuous outcomes, including the primary effectiveness measure (RAS-DS) and secondary measures, will be analysed using linear mixed-effects models with fixed effects for treatment group, time and the group×time interaction, site and caseload group (FEP versus ultra-high risk) to reflect the stratified randomisation. Random intercepts for participants will account for within-participant correlation. A sensitivity analysis will examine a model including a random intercept for site if sufficient numbers per site permit stable estimation; sites recruiting no participants will drop out of the factor, and sites recruiting fewer than five participants will remain in the main analysis, but will be excluded in an additional sensitivity analysis. Consistent with the addendum to the International Council for Harmonisation (ICH) E9 harmonised guideline on statistical principles for clinical trials, ICH E9(R1), the handling of intercurrent events and missing data will follow the estimand framework prespecified in the statistical analysis plan.^
59,60
^ For the primary effectiveness estimand, we will apply a hybrid approach that recognises both participants’ capacity to continue treatment and the practical constraints that may limit their ability to do so. In this method, intercurrent events related to treatment tolerability (e.g. withdrawal owing to adverse effects) will be handled with a treatment-policy strategy (intention to treat) and events related to contextual or service factors (e.g. service disruption) will be handled using a hypothetical strategy, treating outcomes as if treatment had continued, implemented via multiple imputation after removing outcome observations post intercurrent events (ICE).^
61–63
^ We will conduct a range of sensitivity and exploratory analyses, including (a) a treatment policy estimator, using multiple imputation for all missing data; (b) a conservative estimator, using baseline-observation-carried-forward for missing 12-week outcomes; (c) a sensitivity analysis excluding sites with very low recruitment and (d) exploratory analyses of potential dose–response relationships. Full analytical specifications, including model diagnostics and estimand definitions, are detailed in the statistical analysis plan.

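### The primary mixed model as published has no baseline RAS-DS term or common-baseline constraint, so it uses the collected baseline inefficiently

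*Protocol article*

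**What the plan says.** The Statistical analysis section of the protocol article gives one model for the continuous outcomes, primary and secondary: "linear mixed-effects models with fixed effects for treatment group, time and the group×time interaction, site and caseload group". It adds that "Random intercepts for participants will account for within-participant correlation". The two stratification factors are therefore in the model. A baseline score is not named as a covariate, and nothing says that the arms share a baseline mean.

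The baseline score exists. Under Outcomes, "RAS-DS outcomes will be measured at baseline, 12 weeks post baseline (primary end-point) and 52 weeks post baseline".

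The Sample size and power section bases the trial on a "seven-point difference in RAS-DS score, s.d. = 15, Cohen’s *d* = 0.47". "The total planned sample size is 260 participants (130 per arm"), and "The sample size calculation also assumes up to 20% attrition, an intracluster correlation coefficient of 0.02" with "an average cluster size of 20, with parameter optimisation undertaken to confirm feasibility under these assumptions". No correlation between baseline and 12 weeks is mentioned.

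The section on analysis closes by saying that "Full analytical specifications, including model diagnostics and estimand definitions, are detailed in the statistical analysis plan".

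**The concern.** Suppose baseline is one of the levels of time and group has its own main effect. The model then estimates a separate baseline mean in each arm, although randomisation makes those means equal in expectation. The 12-week group×time term becomes a comparison of change scores. The 12-week marginal difference from the same fit is close to a comparison of follow-up scores alone. Both are less precise than an analysis that adjusts for baseline or constrains the baseline means to be equal.

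At stake is the width of the confidence interval for the primary effectiveness outcome. In one configuration the power of the analysis could also fall below the level on which the sample size rests.

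**Working it through.** **Inputs from the article:** difference 7, s.d. 15, 130 per arm, 20% attrition (so 104 per arm followed up and 26 with baseline only), intracluster correlation 0.02, average cluster size 20, visits at baseline, 12 and 52 weeks.

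**Assumed:** two-sided alpha 0.05; 80% power for the reproduction; one common correlation r between visits (compound symmetry, as a random intercept implies), taken from 0.3 to 0.7; those lost to follow-up contribute baseline only.

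**The plan's own figure.** A two-sample t-test for 7/15 = 0.467 needs 74 per arm. The design effect is 1 + 19×0.02 = 1.38. Then 74×1.38/0.8 = 127.7, so 128 per arm and 256 in total, within 2% of 260. The sample size therefore fits an unadjusted 12-week comparison at about 80% power and takes no credit for baseline. With 104 per arm and the design effect, that comparison has SE √(2×225×1.38/104) = 2.44 and power of about 82%.

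**Variances of the 12-week contrast, without design effect** (2×15² = 450):

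- group×time: 450×[(1−r)²/130 + (1−r²)/104]
- 12-week marginal difference, same model: 450×[r²/130 + (1−r²)/104]
- common baseline mean: 450×(1−r²)/104

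A generalised least squares calculation over the three visits gives the same values. At r = 0.5, group×time is 450×(0.25/130 + 0.75/104) = 4.11, SE 2.03. The constrained model is 450×0.75/104 = 3.25, SE 1.80.

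The variance ratios to the constrained model are 1 + 0.8(1−r)/(1+r) for group×time and 1 + 0.8r²/(1−r²) for the marginal difference, where 0.8 = 104/130. Both exceed 1 for every r strictly between 0 and 1.

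| r | SE group×time | SE marginal | SE constrained | Ratio, group×time | Ratio, marginal |
|---|---|---|---|---|---|
| 0.3 | 2.37 | 2.06 | 1.98 | 1.43 | 1.08 |
| 0.4 | 2.21 | 2.05 | 1.91 | 1.34 | 1.15 |
| 0.5 | 2.03 | 2.03 | 1.80 | 1.27 | 1.27 |
| 0.7 | 1.59 | 1.98 | 1.49 | 1.14 | 1.77 |

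**Power.** Multiply each SE by √1.38 = 1.175 and take Φ(7/SE − 1.96):

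| r | Group×time | Constrained |
|---|---|---|
| 0.3 | 71% | 85% |
| 0.4 | 77% | 88% |
| 0.5 | 84% | 91% |
| 0.7 | 96% | 98% |

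Without the design effect, group×time at r = 0.3 has power Φ(7/2.37 − 1.96), about 84%.

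**Break-even with the comparison behind 260.** Group×time is less precise than an unadjusted comparison of 104 per arm when (1−r)²/130 > r²/104. That is (1−r)/r > √1.25 = 1.118, or r < 0.47.

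**The case against.** The strongest reply is that this is a condensed article that refers the full specification to a statistical analysis plan, and that plan may include a baseline term. This limits the point to the model as published. It does not remove it, because the article does not stay silent. It lists the fixed effects down to the stratification factors, and the list has no baseline term.

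Four stronger readings are tempting, and the article does not support them.

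- A reader might infer that the baseline is thrown away. If baseline is a level of time, the group×time term is a change-from-baseline comparison. It uses the baseline, though not optimally, and for r above about 0.47 it is more precise than the comparison behind 260. Only if time covered 12 and 52 weeks alone would the baseline go unused, and the article does not say so.
- A reader might infer bias from chance baseline imbalance. Over randomisations the listed model is unbiased, and imbalance shows up as variance.
- A reader might infer that the trial is underpowered. That needs three things together: the interaction as the primary contrast, r below about 0.5, and the 1.38 design effect. The article gives neither of the first two. The third is open to question, because individuals are randomised within site and site is a fixed effect, so the inflation may not apply to this contrast.
- A reader might infer that the random intercept must be replaced by an unstructured covariance, or that the primary contrast is missing. An article may leave both to the analysis plan, and the article does fix RAS-DS at 12 weeks as the primary end-point.

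**Conclusion.** The point holds as one of efficiency. As published, the primary model is less precise than a baseline-adjusted or constrained model under either 12-week contrast. For group×time the excess variance runs from 43% at r = 0.3 to 14% at r = 0.7. For the marginal difference it runs from 8% to 77% over the same range. These figures assume s.d. 15, compound symmetry, 130 per arm at baseline with 104 followed up, and a correlation that the article does not state.

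Validity is not in question, and 260 did not rely on a gain from baseline. The change is worth making because the data are already collected and the improvement costs nothing. If the statistical analysis plan already adjusts for baseline, only the article's description needs correcting.

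**What to change.** For the RAS-DS and each secondary outcome with a baseline measure, choose one of two forms and state it:

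- keep baseline as a response in the longitudinal model, with the baseline means constrained to be equal across arms and treatment terms only after baseline; or
- model the post-baseline scores with the baseline value as covariate and a baseline×time term.

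Keep site and caseload group in either form. Treatment terms apply at 12 and 52 weeks where both are measured. For the CSQ-8 and the SOFAS they apply at 12 weeks only, because Table 2 ticks no 52-week assessment for them; with a single follow-up visit the baseline×time term drops out.

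The cost is one sentence in the protocol and the statistical analysis plan, made before unblinded data are seen. It needs no new data and no change to the sample size.

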### Randomisation and blinding

Randomisation will be performed centrally with the REDCap randomisation module, with permuted blocks of random size (2, 4) and stratification by site and caseload type (FEP versus ultra-high risk). Allocation will be concealed from outcome assessors and statisticians. Participants and peer coaches cannot be blinded to allocation, but assessors will complete a blinding questionnaire post intervention, and any suspected breaches will be documented for sensitivity analyses.

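### If the 12-week effect is read from the group×time term, the additive site and caseload terms and the random site intercept have almost no influence on it; adding site×time and caseload×time is a free improvement with a small gain

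*Protocol article*

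**What the plan says.** All places are in the protocol article.

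- **Randomisation and blinding:** randomisation is stratified by site and by caseload (FEP or ultra-high risk).
- **Outcomes:** "RAS-DS outcomes will be measured at baseline, 12 weeks post baseline (primary end-point) and 52 weeks post baseline".
- **Statistical analysis:** the primary model has terms for arm, visit and their interaction, and also "site and caseload group (FEP versus ultra-high risk) to reflect the stratified randomisation". The last two enter as main effects only. "Random intercepts for participants will account for within-participant correlation". No baseline covariate is listed.
- **Statistical analysis, on site:** "A sensitivity analysis will examine a model including a random intercept for site if sufficient numbers per site permit stable estimation". A further analysis leaves out sites with fewer than five participants.
- **Sample size and power:** "We assumed a seven-point between-group difference on the RAS-DS at 12 weeks".

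Full analytical specifications and estimand definitions are deferred to a statistical analysis plan that is not shown.

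**The concern.** A model with group×time, a participant intercept and no baseline covariate is ordinarily read as having baseline among the responses, with the 12-week group×time coefficient as the treatment effect. That coefficient compares within-person change between arms. A term that is constant over a person's visits cannot enter a within-person change. On this reading the site and caseload terms do not do the work the section gives them.

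Two things are at stake. First, differences between sites or streams in 12-week change stay in the residual, although stratification balanced them. Such differences are plausible on the article's own account: the introduction describes care of 2–5 years for FEP and up to 12 months for ultra-high risk, and the limitations note that usual care varies across sites. Second, a random-site analysis that agrees closely with the main result would look like evidence of robustness to site, when close agreement is nearly built in.

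**Working it through.** **Inputs from the article.** N = 260 (130 per arm), eight planned sites, SD 15, difference 7 points, ICC 0.02, average cluster size 20, attrition up to 20%, visits at baseline, 12 and 52 weeks.

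**Assumed.** Two-sided 5% level and 80% power; within-person correlation 0.5 or 0.6; a 5-point caseload difference in level; 15% further loss at 52 weeks. Other assumptions are given where used.

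**Step 1: the plan's own figure.** Per arm, 2 × (1.960 + 0.842)² × (15/7)² = 72.1, so 73. The design effect is 1 + 19 × 0.02 = 1.38, and 73 × 1.38 = 100.7, so 101. Then 101/0.8 = 126.3, so 127 per arm, or 254 in total (258 with the t distribution). The stated 260 is reproduced closely, and this point does not affect it.

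**Step 2: algebra.** Write the printed model as

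Y(i,t) = μ + βG + τ(t) + δ(t)G + site + caseload + b(i) + e(i,t).

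Then Y(i,12) − Y(i,0) = τ(12) + δ(12)G + e(i,12) − e(i,0), taking τ and δ as zero at baseline. Site, caseload, any random site intercept and b(i) are gone. With complete data the estimate of δ(12) is the difference in mean change, with SE = √[2σ²(e) × (2/130)]. At correlation 0.6, σ²(e) = 225 × 0.4 = 90, giving √2.769 = 1.66. The 12-week group difference is β + δ(12); it compares people, so the strata terms do enter it.

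**Step 3: complete data.** One simulated trial (correlation 0.5, site ICC about 0.02), fitted three ways:

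| Model | group×time at 12 weeks (SE) | 12-week group difference (SE) |
|---|---|---|
| No strata terms | 3.891 (1.817) | 8.739 (1.939) |
| Fixed site and caseload, as planned | 3.891 (1.817) | 8.833 (1.878) |
| Random site, fixed caseload | 3.891 (1.817) | 8.804 (1.878) |

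Two further trials showed the same exact agreement in the group×time column.

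**Step 4: 20% attrition (40 simulated trials).**
- Adding fixed site and caseload moved the group×time estimate by 0.07 points on average, at most 0.41.
- Replacing fixed site by random site moved it by 0.04 on average, at most 0.12.
- The mean SE was 2.037 in all three models.
- With baseline as a covariate, adding the strata moved the 12-week effect by 0.12 on average, at most 0.41.

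**Step 5: what time-specific strata terms would gain.** The article's only clustering figure is the ICC of 0.02, which is 15 × √0.02 = 2.1 points. Assume site variation in change has that SD. The variance of change at correlation 0.6 is 2 × 225 × 0.4 = 180, so the SE ratio is √[(180 + 4.5)/180] = 1.012, or about 1%.

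Larger assumed heterogeneity, 208 completers, 6,000 simulated trials per row:

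| Site SD in change; stream difference in change | SE, planned | SE with site×time and caseload×time | Ratio |
|---|---|---|---|
| 0; 0 | 1.860 | 1.861 | 1.00 |
| 3; 5 | 1.918 | 1.858 | 1.03 |
| 4; 8 | 1.976 | 1.857 | 1.06 |
| 5; 10 | 2.044 | 1.862 | 1.10 |

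A separate, smaller simulation (25 trials per scenario, all 260 participants, 30% ultra-high risk) gave ratios of 1.711/1.672 = 1.02 at (3; 5) and 1.796/1.659 = 1.08 at (5; 10). With 20% of follow-up missing the ratios were 1.870/1.826 = 1.02 and 1.936/1.807 = 1.07. A site SD in change of 3 to 5 corresponds to an ICC in change of 9/189 = 0.05 to 25/205 = 0.12, at or above the top of the 0.01–0.05 range that the article cites.

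**The case against.** The strongest reply is that the article never says the effect is the group×time coefficient. It sizes the trial on a between-group difference at 12 weeks, and for the model-based version of that difference the strata terms contribute even with complete data (Step 3). They also contribute if baseline is a covariate. The unseen analysis plan may specify either. This stands, and it makes the point conditional. It does not remove it, because the article prints the fixed and random effects without a baseline covariate, and the ordinary reading of that list is the one on which the terms drop out.

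Three stronger conclusions are tempting, and the documents do not support them.

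- **That the random-site analysis cannot alter the result.** This is exact only with complete or fully imputed data. With the attrition the plan expects, small shifts occur. Imputation of all missing data is named only for a sensitivity analysis.
- **That the analysis ignores the stratification.** The model contains both factors. Where they drop out, within-person change has already removed stratum differences in level. Only differences in change are left. In the heterogeneous scenarios, 95% intervals covered 95.4% to 96.7%, so the planned analysis is slightly conservative, not invalid.
- **That the effect is materially biased.** A shift of about 0.4 points can be constructed. With 30% ultra-high risk, retention in that stream of 90% v. 60% by arm and 80% in FEP, the ultra-high-risk share of completers is 0.27/0.83 = 0.325 v. 0.18/0.74 = 0.243. Multiplied by a 5-point stream difference in change, that gives 0.41. The article gives no basis for those retention rates.

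It is also fair that additive strata terms are conventional, that random site effects on change may be hard to estimate with eight sites, and that the analysis excluding very small sites is a separate check that can differ from the main result.

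**Conclusion.** The point holds conditionally. With baseline RAS-DS as a response and the 12-week group×time coefficient as the effect, the additive site and caseload terms and the random site intercept contribute nothing with complete or fully imputed data, and almost nothing at 20% attrition. The model then leaves stratum differences in change unadjusted, and agreement between the fixed-site and random-site models is no real evidence of robustness to site.

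The cost is modest: about 1% of the standard error if site variation in change matches the plan's ICC, and about 3–10% only under the larger site and stream differences assumed above. The within-person correlation, the heterogeneity in change and the simulated drop-out patterns are assumptions, not figures from the article. Severity is minor to moderate: a free improvement in the main model, and a sensitivity analysis that needs replacing or relabelling.

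**What to change.** 1. Add site×time and caseload×time to the primary model, with time categorical and very small sites pooled if needed. Put the same terms in the imputation model.
2. Replace the random-site-intercept analysis with one that lets the 12-week change or treatment effect vary by site, for example fixed or random site-by-group effects at 12 weeks with small-sample degrees of freedom. Otherwise, stop presenting it as a check of robustness to site.
3. If the analysis plan takes the model-based 12-week group difference as the effect, or uses baseline as a covariate, say so in the Statistical analysis section. The strata terms then contribute as they stand, and the terms in item 1 do not worsen the 12-week group contrast.

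The cost is a line of model wording and, with eight sites and two streams, 7 + 1 = 8 fixed-effect degrees of freedom per follow-up visit. No new data are needed, and without heterogeneity precision is essentially unchanged (SE 1.861 v. 1.860).

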## Aims and research questions

### Aim 1: Experimentally evaluate the effects of MyPREPED versus usual care (control)

We aim to evaluate the impact of the MyPREPED intervention, on mental health recovery alongside other outcomes relating to mental health quality of life, and psychosocial and functional outcomes (see section ‘Outcomes’), by asking the following questions:Is MyPREPED more effective than usual care in improving mental health recovery at the primary end-point (12 weeks post baseline)?Is MyPREPED more effective than usual care in improving secondary outcomes at the primary end-point (12 weeks post baseline)?Are effects maintained at 52 weeks post baseline?

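### The mixed model handles within-person correlation only through a participant random intercept, which assumes one variance and one correlation across 0, 12 and 52 weeks; the documents do not support that assumption, and the size and direction of any error are unknown

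*Protocol article*

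**What the plan says.** The Statistical analysis section of the protocol article specifies linear mixed models for the RAS-DS and the secondary continuous outcomes, with "fixed effects for treatment group, time and the group×time interaction, site and caseload group". On the repeated measurements it says: "Random intercepts for participants will account for within-participant correlation". The only other random effect named is an intercept for site, in a sensitivity analysis. The sensitivity analyses listed there concern the estimand, missing data, low-recruiting sites and dose-response. None of them relaxes the within-person structure.

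The visits are set in the Outcomes section: "RAS-DS outcomes will be measured at baseline, 12 weeks post baseline (primary end-point) and 52 weeks post baseline". The third question of Aim 1 uses the last visit: "Are effects maintained at 52 weeks post baseline".

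The section closes by deferring detail: "Full analytical specifications, including model diagnostics and estimand definitions, are detailed in the statistical analysis plan". That plan is not at hand.

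**The concern.** A single participant intercept with independent, equal-variance residuals is compound symmetry: one variance for all visits and one correlation for all pairs. The gaps here are 12, 40 and 52 weeks. Participants enter within six months of planned discharge, so discharge falls between baseline and week 52, on one side or the other of week 12. The section on transition from EIPS describes heightened vulnerability after discharge and widely differing care pathways. Equal correlation over all three gaps and constant spread are therefore doubtful, and the article offers no support for them.

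If the assumption fails, the model averages the variances and correlations and applies the average to every contrast, so model-based standard errors can be wrong. At stake are the precision of the 12-week result and the error rate of the 52-week maintenance question. A 52-week interval that is too narrow would make maintenance too easy to claim. The same model serves the secondary continuous outcomes.

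**Working it through.** **Inputs from the article.** 130 per arm (260 in total); "seven-point difference in RAS-DS score, s.d. = 15"; the calculation "assumes up to 20% attrition, an intracluster correlation coefficient of 0.02"; average cluster size 20. Significance level and power are not stated in the article; 5% two-sided and 80% are assumed here.

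**The plan's own figure.** n per arm = 2 × (1.96 + 0.842)² × 15² / 7² = 72.1, so 73. Design effect 1 + 19 × 0.02 = 1.38; 73 × 1.38 = 100.7, so 101. Dividing by 0.80 gives 126.3, so 127 per arm, or 254 in total. The t-test version gives 258. The planned 260 is reproduced closely. The calculation uses one standard deviation and no between-visit correlation, so it says nothing about the covariance over time.

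**Formula.** The group effect is free at baseline, so the group×time term is a difference in change from baseline. With complete data and equal SDs, its standard error is 2 × SD × √((1 − ρ)/n), where ρ is the correlation of that visit with baseline. The random-intercept model replaces ρ by the average of the three correlations.

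**Worked example.** Assume correlations (0-12, 0-52, 12-52) of 0.70/0.40/0.50, SD 15 and n = 130.
- Average correlation: (0.70 + 0.40 + 0.50)/3 = 0.533.
- Model SE at both visits: 30 × √(0.467/130) = 1.80.
- True SE at 12 weeks: 30 × √(0.30/130) = 1.44; ratio 1.25.
- True SE at 52 weeks: 30 × √(0.60/130) = 2.04; ratio 0.88.
- False-positive rate at 52 weeks: 2 × (1 − Φ(1.96 × 0.882)) = 8.4%.

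**With 20% lost after baseline.** Here the compound-symmetry fit is the one that maximises the expected normal likelihood, and its model SE is compared with the true SE. All correlations are assumptions; SD is 15 throughout.

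| Correlations 0-12 / 0-52 / 12-52 | Change at 12 wk: model v true SE (ratio) | Change at 52 wk: model v true SE (ratio) | 52-wk false-positive rate |
|---|---|---|---|
| 0.65/0.55/0.60 | 1.82 v 1.71 (1.07) | 1.82 v 1.93 (0.95) | 6.4% |
| 0.70/0.50/0.60 | 1.82 v 1.59 (1.15) | 1.82 v 2.03 (0.90) | 7.8% |
| 0.70/0.40/0.50 | 1.96 v 1.59 (1.23) | 1.96 v 2.21 (0.89) | 8.2% |
| 0.60/0.60/0.60 | 1.82 v 1.82 (1.00) | 1.82 v 1.82 (1.00) | 5.0% |
| 0.50/0.45/0.70 | 1.93 v 2.03 (0.95) | 1.93 v 2.12 (0.91) | 7.5% |

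With 30% lost at 52 weeks (assumed), 0.70/0.40/0.50 gives 1.94 against 1.59 at 12 weeks, and 2.04 against 2.32 at 52 weeks (ratio 0.88, false-positive rate 8.5%).

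**Arm difference at a visit.** With equal SDs and complete data the error is nil. With 20% loss the ratios in the three decay rows are 1.01-1.02 at 12 weeks and 0.99 at 52 weeks. With 30% lost at 52 weeks the lowest 52-week ratio is 0.97.

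**Unequal SDs, 20% loss.**
- SDs 13/17/15 with 0.60/0.50/0.60: change ratios 0.99 and 0.99, but 0.88 for the arm difference at 12 weeks.
- SDs 12/15/18 with 0.70/0.50/0.60: 0.82 for the arm difference at 52 weeks (false-positive rate about 11%).
- SDs 18/15/12 with 0.70/0.50/0.60: 1.26 for the arm difference at 52 weeks.

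These figures are large-sample, leave out the site design effect, and do not simulate the planned multiple imputation. If the same model is fitted to each imputed data set, its model-based standard error still enters the within-imputation variance.

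**The case against.** A reader might infer that the 12-week interval is bound to be too wide and the 52-week interval too narrow. The documents do not support that. It needs correlation that decays with the gap, similar SDs at all visits, and the change contrast as the reported effect. The article establishes none of these. Post-discharge vulnerability is not a statement about the variance or correlation of RAS-DS scores. Discharge may also fall before week 12, which could weaken the 0-12 correlation and fits the 0.50/0.45/0.70 case, where both intervals are too narrow.

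The sample-size section frames the effect as a between-group difference at 12 weeks, which reads naturally as the arm difference at that visit. For that contrast, with equal SDs, little is wrong. The analysis section does not say which contrast is reported.

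Under decay the primary result is also barely harmed. With 0.70/0.40/0.50 and 20% loss, power for 7 points is Φ((7 − 1.96 × 1.96)/1.59), about 98%, against Φ(7/1.59 − 1.96), about 99%, before any design effect. The false-positive concern lies mainly at 52 weeks, which is not the primary end-point.

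Finally, the unseen analysis plan may add a residual structure or robust standard errors. That would remove the problem, and it limits the claim to the model as the article describes it.

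All of this stands against a claim of known direction. It does not defend the assumption itself: the article affirmatively names the random intercept as what handles the correlation, and validity then rests on an equality that the trial has no need to assume.

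**Conclusion.** The point holds in conditional form. As described, the model assumes one variance and one correlation across three unequally spaced visits that span discharge, and no listed sensitivity analysis relaxes this.

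The size and direction of any error are not known. Under the assumed decay patterns with similar SDs, the change interval is roughly 7-23% too wide at 12 weeks and 5-12% too narrow at 52 weeks, with a 52-week false-positive rate of about 6-9%. If correlations and variances are equal there is no error, and under other patterns the 12-week direction reverses. For the arm difference at a visit with equal SDs the error is about 1-3% or less; it returns, in either direction, if variances differ by visit. All of this presumes independent, equal-variance residuals and model-based standard errors.

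The change is worth making because it removes the assumption at almost no cost, not because the primary analysis is shown to be invalid.

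**What to change.** Fit the continuous outcomes with an unstructured covariance matrix over the three visits in place of the participant random intercept: time as a categorical factor, REML, Kenward-Roger degrees of freedom. State that the between-arm contrasts at 12 and 52 weeks are reported from that model. Keep the random-intercept model as the fallback if the unstructured one does not converge.

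The cost is about one sentence in the protocol and the analysis plan, and six covariance parameters instead of two, which 260 participants can support. No new data are needed. The 52-week intervals may become slightly wider. Compound symmetry is a special case of the unstructured model, so little is lost if the present assumption turns out to be true.
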